### Statistical plan and data analysis

A fully detailed statistical analysis plan will be developed and published before enrolment is initiated. General principles are outlined below.  

The primary analysis of all outcomes will be based on the intention-to-treat population.

Mixed-effects linear regression and mixed-effects logistic regression will be used to analyse the continuous and dichotomous co-primary outcomes, respectively. In the regression models, we will adjust for the three stratification variables: ‘site’ will be included as a random effect, while ‘gestational age below or above 34 weeks of postmenstrual age’ and ‘group allocation’ will be included as fixed effects. Due to the relatively large sample size, we do not expect major unequal baseline characteristics in the two groups, and therefore, we do not a priori plan to include baseline variables as covariates in the statistical analyses. However, if baseline covariates will be unequal between the two groups, we plan to add sensitivity analyses adjusting for unequal baseline covariates to assess whether such baseline differences lead to different results. To correct for multiple testing, the threshold for statistical significance will undergo Bonferroni adjustment, and thus a *p*-value of 0.025 for each of the primary outcomes is chosen. The superiority of the intervention will only be claimed if at least one of the two co-primary outcomes is statistically significant. All other outcome results will be considered hypothesis-generating only.

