### Sample size

To test a reduction in death or moderate to severe neurodevelopment disability from 20 to 16% between the usual care group versus the cerebral oximetry group (a relative risk reduction of 20%), a total of 1500 participants in each group and a total of 3000 participants is needed. This calculation on the dichotomized, composite primary outcome is based on an alpha level of 2.5% and a power of 73%.

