#### Countermeasures

A primary outcome at 90 days could be used, and the 2-year follow-up could be secondary. Given the lack of reliable routinely used measures of brain injury in this heterogenous population, the best candidate for this would be ‘days alive out of hospital within 90 days’.

‘High probability of loss to follow-up’ could be used as an exclusion criterium. This was discussed during the draft of the protocol but will not be done, since it would be difficult to operationalise and would reduce the generalisability.

Follow-up could be run by the SafeBoosC project team (central follow-up) to spare the work of principal investigators at each site, but this will involve transfer of patient identity and contact information from sites in all countries to the trial centre in Denmark, which will require separate parental consent and will in principle increase privacy risks.

Some loss to follow-up is unavoidable, and in a 2-year follow-up of a mixed group of newborn infants, this may be significant. The loss to follow-up is likely to be different among children who do well and those who do not. This, however, will not cause bias unless, what is much less likely, the loss is also different among those who had cerebral oximetry and those who did not. A loss to follow-up will always reduce the statistical power. If the loss amounts to as much as 20%, the power of the dichotomous co-primary outcome will be reduced to 62%, and the power of the continuous co-primary outcome will still be more than 95%. One way to account for potential loss to follow-up and thereby missing data for the primary outcome is to increase the original sample size for instance from 3000 to 3750 participants to account for a 20% loss to follow-up. This would increase the statistical power of the primary outcome. However, it is difficult a priori to estimate loss to follow-up. Also, we fear that this could be a pretext for inaction to ‘allow’ missing data during the execution of the trial among the many partners. Additionally, increasing the sample size does not address the risk of bias, which is the ‘true’ problem when loss to follow-up is substantial. To account for missing data in our statistical analysis, we will use the methods described by Jakobsen et al. [29].

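### Fixed Bonferroni at 0.025 is valid but inefficient: Holm's procedure would let the composite be claimed more often once PARCA-R is significant (about 81% against 73% power if both planned effects hold)

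*Protocol article*

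**What the plan says.** Three sections of the protocol article matter here.

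- **Statistical plan and data analysis** sets the multiplicity rule: "To correct for multiple testing, the threshold for statistical significance will undergo Bonferroni adjustment", with a p-value of "0.025 for each of the primary outcomes is chosen". The claim rule follows: "The superiority of the intervention will only be claimed if at least one of the two co-primary outcomes is statistically significant". No step-down or passing on of alpha is described.
- **Sample size** plans to detect "a reduction in death or moderate to severe neurodevelopment disability from 20 to 16" per cent with 1500 per group, and says that the calculation "is based on an alpha level of 2.5% and a power of 73" per cent. **Power of the continuous primary outcome** gives more than 98% for a 3-point PARCA-R difference (SD 18, 8% deaths) at the same alpha.
- **Challenge 3, Countermeasures** considers 20% loss to follow-up. There, "the power of the dichotomous co-primary outcome will be reduced to 62" per cent, while PARCA-R keeps more than 95%.

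**The concern.** The two co-primary outcomes are powered very unequally. PARCA-R is almost certain to succeed at its planned effect, whereas the composite is below the usual 80% even with complete follow-up. Yet the composite matters more to patients: the article itself says, in the countermeasure to Challenge 1, that the neurodevelopment measure is not directly patient-relevant.

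Under a single-step Bonferroni rule, the 0.025 spent on PARCA-R is lost to the composite even when PARCA-R has been shown to differ. With a clearly significant PARCA-R result and a composite p-value of 0.03, the composite would have to be reported as not significant. Holm's procedure would declare it significant at the same familywise error. Challenge 3 argues against enlarging the sample, so a gain that needs no extra newborns deserves attention.

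**Working it through.** **Inputs from the article.** Composite 20% against 16%; 1500 per group; alpha 0.025 per outcome; PARCA-R difference 3 points, SD 18; 8% deaths, so 1500 × 0.92 = 1380 per group with a score. With 20% loss: 1200 per group, and 1200 × 0.92 = 1104 with a score. (The article labels 3 points as d = 0.2; 3/18 is 0.17. The points and SD are used here because they reproduce the stated power.)

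**Assumptions.** Two-sided tests: the article does not state this in the power section, but one-sided 2.5% would give 81.4%, not the stated 73%. The correlation between the two test statistics is not given, so 0 to 0.6 is used. It should be positive, because a very low PARCA-R score is itself one way of meeting the composite.

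**Step 1: reproduce the stated power.** Critical values: 2.241 for two-sided 0.025 and 1.960 for two-sided 0.05. Φ is the standard normal distribution function.

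- Composite: SE = √[(0.20×0.80 + 0.16×0.84)/1500] = √(0.2944/1500) = 0.01401. Expected Z = 0.04/0.01401 = 2.855. Power at 0.025 = Φ(2.855 − 2.241) = 73.0% (stated 73%).
- Composite, 20% loss: expected Z = 0.04/√(0.2944/1200) = 2.554. Power = Φ(2.554 − 2.241) = 62.3% (stated 62%).
- PARCA-R: expected Z = 3/(18√(2/1380)) = 4.378. Power = Φ(4.378 − 2.241) = 98.4% (stated more than 98%). With 1104 per group: 95.3% (stated more than 95%).

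All the stated figures reproduce.

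**Step 2: error control under Holm.** Test the smaller p-value at 0.025 and, only if it is significant, the larger at 0.05. If both nulls are true, a false claim needs one p-value at or below 0.025, which has probability at most 2 × 0.025 = 0.05. If only one null is true, it can be rejected only if its own p-value is at or below 0.05. Neither argument uses the correlation.

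**Step 3: power for the composite under Holm.** With Z1 the composite and Z2 the PARCA-R statistic,

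power = P(Z1 > 2.241) + P(1.960 < Z1 ≤ 2.241 and Z2 > 2.241).

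At correlation 0 the second term is a product. The composite tested at a full 0.05 has power Φ(2.855 − 1.960) = 81.5%, so the middle band holds 0.8147 − 0.7303 = 0.0844.

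- Planned effects: 0.7303 + 0.0844 × 0.984 = 81.3%.
- Planned effects, 20% loss: 0.6226 + (0.7237 − 0.6226) × 0.953 = 71.9%.

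Bivariate-normal probabilities for correlation 0 to 0.6 give:

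| True PARCA-R difference | PARCA-R power at 0.025 | Composite, Bonferroni | Composite, Holm |
|---|---|---|---|
| 3 points | 98.4% | 73.0% | 81.3% |
| 2 points | 75.1% | 73.0% | 78.2–79.4% |
| 1.5 points | 47.9% | 73.0% | 75.3–77.1% |
| 1 point | 21.7% | 73.0% | 73.6–74.9% |
| 0 | 1.25% (in the favourable direction) | 73.0% | 73.0–73.1% |
| 3 points, 20% loss | 95.3% | 62.3% | 71.8–72.0% |
| 2 points, 20% loss | 64.4% | 62.3% | 67.8–68.8% |

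**Step 4: the superiority rule.** The chance that at least one outcome is significant is the same under both procedures, because Holm adds a rejection only after the other outcome has passed 0.025. At the planned effects it is 98.6% to 99.6%.

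**Step 5: for scale.** Reaching 80% for the composite at a fixed 0.025 would take about 1753 per group, that is 2 × (1753 − 1500) = 506 more newborns.

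**The case against.** Much of the case for leaving the plan alone is sound.

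- **Bonferroni is valid and consistently applied.** A reader might infer that the multiplicity control is wrong or the power figures mistaken. The article does not support that: the 5% is controlled and every stated power reproduces. What remains is avoidable inefficiency.
- **The trial's success criterion gains nothing.** A reader might infer that Holm makes a positive trial more likely. It does not (Step 4). Every added rejection comes when superiority has already been claimed through PARCA-R. The gain is a second, more patient-relevant claim.
- **The gain is conditional on PARCA-R.** It disappears when PARCA-R shows no effect, which is where the composite would have to stand alone. A reader might also take 81% as the power given that PARCA-R is significant. It is unconditional power with a true 3-point effect. With a 2-point effect and correlation 0.6, unconditional power is 78%, whereas power given a significant PARCA-R result is about 90%.
- **Bonferroni has matching confidence intervals.** This is its one real advantage. In the only cases where Holm differs, with a composite p-value between 0.025 and 0.05, the 97.5% interval will include no effect although the test rejects. Challenge 1 reasons from confidence intervals, so this mismatch must be handled openly.

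These points limit the size of the recommendation. None gives Bonferroni an advantage in error control or power.

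**Conclusion.** The point holds as a cheap improvement, not as the correction of an error. The gain for the composite is about 8 percentage points with full follow-up and about 10 with 20% loss, provided that both planned effects are true. It is 5 to 6 points if the true PARCA-R difference is 2 points, 2 to 4 at 1.5 points, at most 2 at 1 point, and essentially nil at 0 (all with full follow-up). These figures rest on the article's planning values, two-sided testing and an assumed correlation of 0 to 0.6. At the planned effects the correlation hardly matters. Holm does not bring the composite to 80% if follow-up falls by 20%. The statistical analysis plan is not at hand; if it already specifies a step-down test, the article's sentence simply needs to be brought into line with it.

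**What to change.** Before unblinding:

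1. Replace the Bonferroni sentence under Statistical plan and data analysis with: *The two co-primary outcomes are tested by Holm's procedure: the smaller p-value against 0.025 and, if significant, the larger against 0.05.*
2. Report Holm-adjusted p-values and give both 95% and 97.5% confidence intervals. State that the decision rests on the Holm test, since a 97.5% interval can include no effect when Holm rejects at a p-value between 0.025 and 0.05.
3. Restate composite power under Sample size and in Challenge 3, Countermeasures, as: *73% under Bonferroni; about 81% under Holm if the planned effects on both outcomes hold (62% and about 72% with 20% loss to follow-up).*

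The cost is a few sentences in the protocol and analysis plan. Sample size, outcomes, data collection and regression models stay as they are. The one drawback is that the intervals do not match the step-down test exactly.

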**Methods/design:**

SafeBoosC-IIIv is an investigator-initiated, multinational, randomised, pragmatic phase-III clinical trial. The inclusion criteria will be newborns with a gestational age more than 28 + 0 weeks, postnatal age less than 28 days, predicted to require mechanical ventilation for at least 24 h, and prior informed consent from the parents or deferred consent or absence of opt-out. The exclusion criteria will be no available cerebral oximeter, suspicion of or confirmed brain injury or disorder, or congenital heart disease likely to require surgery.

A total of 3000 participants will be randomised in 60 neonatal intensive care units from 16 countries, in a 1:1 allocation ratio to cerebral oximetry versus usual care. Participants in the cerebral oximetry group will undergo cerebral oximetry monitoring during mechanical ventilation in the neonatal intensive care unit for as long as deemed useful by the treating physician or until 28 days of life. The participants in the cerebral oximetry group will be treated according to the SafeBoosC treatment guideline. Participants in the usual care group will not receive cerebral oximetry and will receive usual care. We use two co-primary outcomes: (1) a composite of death from any cause or moderate to severe neurodevelopmental disability at 2 years of corrected age and (2) the non-verbal cognitive score of the Parent Report of Children’s Abilities-Revised (PARCA-R) at 2 years of corrected age.

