### Power of the continuous primary outcome

A power analysis for the continuous primary outcome, i.e. a non-verbal cognitive score of PARCA-R, shows that with a sample of 1500 in each group and an expected rate of death of 8%, and a standard deviation of the PARCA score of 18 points, the power will be more than 98% to detect a difference of 3 points (Cohen’s *d* = 0.2 standard deviation), at an alpha of 2.5%.

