#### Countermeasure

A measure of neurodevelopment was included as a co-primary outcome. The power to detect a small effect will be high. This is not directly patient-relevant, but a null-finding may have more impact on clinical practice.

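### Superiority may be claimed on the PARCA-R score alone, but only survivors have that score and mortality has no formal part in the claim

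*Protocol article*

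**What the plan says.** The claim rule stands under Statistical plan and data analysis: "The superiority of the intervention will only be claimed if at least one of the two co-primary outcomes is statistically significant". For multiplicity, "the threshold for statistical significance will undergo Bonferroni adjustment", which gives 0.025 per co-primary. The section sets no condition on the other co-primary or on mortality, and it treats every other outcome as hypothesis-generating. The Outcomes section lists 2-year all-cause mortality among the exploratory outcomes.

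The first co-primary is a composite that counts death. The second is the PARCA-R non-verbal score, from a parental questionnaire at 2 years of corrected age; no value is given for children who die. Its power is worked out "with a sample of 1500 in each group and an expected rate of death of 8" per cent, an SD of 18 and a difference of 3 points, and is put at more than 98%. The composite is "based on an alpha level of 2.5% and a power of 73" per cent.

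On the score itself, the countermeasure to Challenge 1 says: "This is not directly patient-relevant".

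**The concern.** Survival is measured after randomisation and is one of the things the intervention is meant to change. A comparison of survivors' mean scores is therefore not a comparison of the groups as randomised. If oximetry led to more deaths among the frailest infants, the surviving oximetry children would score higher on average without any child having gained. If it truly helped survivors while costing lives, the score would show the gain and leave out the deaths.

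The composite does count deaths, but the rule does not ask it to agree. It can also stay flat when the extra deaths fall on children who would otherwise have been disabled, since those children count as events either way. PARCA-R is much the better powered of the two outcomes, so a claim resting on it alone is a realistic result of this trial.

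**Working it through.** **Inputs from the protocol.** 1500 per group, allocated 1:1; composite 20% versus 16%; deaths 8%; SD 18; difference 3 points; alpha 0.025 per co-primary, taken as two-sided (critical value 2.241, so 1.25% in the favourable direction).

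**The plan's own figures.**
- Composite: the mean rate is 0.18. The SE under the null is √(2×0.18×0.82/1500) = 0.01403 and under the alternative √((0.16+0.1344)/1500) = 0.01401. Power = Φ((0.04 − 2.241×0.01403)/0.01401) = 72.9%, matching 73%. A one-sided 2.5% test would give 81.4%, so the plan's test is two-sided.
- PARCA-R: survivors are 1500×0.92 = 1380 per group. SE = 18×√(2/1380) = 0.685. Power = Φ(3/0.685 − 2.241) = 98.4%, matching more than 98%. All 1500 would give 99.0%, which also exceeds 98%, so the figure alone does not settle the point. But the 8% death rate has a role in this calculation only if the dead are left out.
- With 20% loss: 62.1% (1200 per group) and 95.3% (1104 per group), as stated under Challenge 3.

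**Selection alone, no cognitive effect (assumed scenarios).** Let deaths under oximetry be d instead of 8%. The extra deaths are a share p = (d − 0.08)/0.92 of those who would have survived. If they would have scored k SD below the mean, the survivors' mean rises by 18·k·p/(1 − p). The SE is 18×√(1/1380 + 1/(1500(1 − d))), and the chance of a significant benefit is 1 − Φ(2.241 − shift/SE).

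| Deaths, usual care vs oximetry | Survivors scored | SE | Shift, k = 1 / 1.5 | Chance of significant benefit |
|---|---|---|---|---|
| 8% vs 9.4% | 1380 / 1358 | 0.688 | 0.29 / 0.43 | 3.4% / 5.3% |
| 8% vs 10% | 1380 / 1350 | 0.689 | 0.40 / 0.60 | 4.8% / 8.5% |
| 8% vs 12% | 1380 / 1320 | 0.693 | 0.82 / 1.23 | 14% / 32% |

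The 9.4% is 8% × 1.18. The 1.18 is borrowed, for illustration, from the upper confidence limit of the preceding trial in extremely preterm infants.

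A second model, in which death falls on the frailest and frailty correlates with the score, gives 4.2%, 8.8%, 23% and 41% at 8% versus 12% for correlations of 0.3, 0.5, 0.8 and 1.0.

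**A real gain in survivors with more deaths (assumed).** With +3 points and 8% versus 12% deaths, Φ(3/0.693 − 2.241) = 98.2%. In a simulation of 2000 trials with a composite rate of 20% in both groups, superiority was claimed in 98%; in 94% it was claimed together with significantly higher mortality (two-sided 5%). At 8% versus 10% the figures are 98.5% and 48%.

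**What a guard would do.** The guard is: no significant harm (two-sided 5%) on the composite or on mortality. These steps use a normal approximation and treat the PARCA-R estimate as independent of the other two.
- Both truly neutral: the composite and death estimates correlate at (0.08 − 0.08×0.20)/√(0.08×0.92×0.20×0.80) = 0.59. Both stay below 1.96 in 95.6% of trials, so about 4% of PARCA-R wins are blocked.
- Planned 20% to 16%: about 0.01% blocked if deaths fall in proportion (8% to 6.4%), and 2.5% if deaths do not change.
- 8% versus 12% deaths with a flat composite: the expected mortality z is 0.04/√((0.0736+0.1056)/1500) = 3.66. It fails to reach 1.96 in about 4% of trials, so about 96% of claims are stopped.
- 8% versus 10% deaths: the expected z is 1.92, so about half of the claims are stopped.

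**The case against.** Several stronger readings are tempting, and the documents do not support them.

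- A reader might infer that a significant result in the wrong direction could count. The rule sentence omits direction, but the word superiority and the hypothesis under Objective (lower composite, higher score) supply it. The Discussion's restatement of the hypothesis is garbled for the score and deserves tidying, no more.
- A reader might infer inflated type I error. Two tests at 0.025 total 0.05; either-or testing is valid.
- A reader might infer that saving impaired infants would hide a benefit. With deaths falling from 8% to 6.4% and the saved infants 1 to 2 SD below the mean, survivors lose 0.3 to 0.6 points. Against a true 3-point effect that still leaves about 96% to 89% power.

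Other objections carry some weight. The rule states a necessary condition and does not oblige anyone to make the claim; but no further condition is given. The large false-win figures need a 50% relative rise in deaths. The preceding trial found a relative risk of 1.03 (0.90 to 1.18), though for death or severe brain injury and in less mature infants. An excess of 8% versus 12% would be significant at 5% in about 96% of trials, so it would be seen. The safety committee monitors mortality at 28 days, but that does not limit a claim made at 2 years.

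How deaths enter the analysis of a score is ordinary content for the statistical analysis plan, and its absence here is not held against the protocol. The claim rule, however, is fixed in this protocol, and an analysis plan that follows it inherits the gap.

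**Conclusion.** The concern holds as a defect of the claim rule: an effect measured only in survivors can establish superiority while mortality has no formal part in the decision. Selection alone is a modest risk at plausible excesses of death (3 to 9% against 1.25% for 8% versus 9.4 to 10%) and a large one (14 to 32%) only at 8% versus 12%. The more serious route is a real gain in survivors beside excess deaths, where the rule would almost always be met. The excess deaths, the score deficits, the correlations and the 3-point gain in that scenario are assumptions; the protocol gives no figures for them. The sample size and alpha need no change on this account.

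**What to change.** Add to the claim rule that, when only PARCA-R is significant, superiority also requires no statistically significant harm (two-sided 5%) on the composite or on 2-year all-cause mortality. State that the PARCA-R result is an effect in survivors and will be reported beside mortality. Prespecify one PARCA-R sensitivity analysis of all randomised infants that ranks death below the lowest score. All of this should be in place before unblinded results are seen.

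The cost is a few sentences and one analysis. About 4% of genuine PARCA-R-only claims would be blocked if composite and mortality are truly neutral, and almost none under the planned effect when mortality falls with it. The guard stops only about half of the claims at 8% versus 10% deaths, which is why the reporting and the death-ranked analysis are needed as well. A stricter guard, requiring that neither estimate be numerically worse, would block about 65% of genuine PARCA-R-only claims in the neutral case (both conditions are met in only 35% of trials) and is hard to justify.

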### Sample size

To test a reduction in death or moderate to severe neurodevelopment disability from 20 to 16% between the usual care group versus the cerebral oximetry group (a relative risk reduction of 20%), a total of 1500 participants in each group and a total of 3000 participants is needed. This calculation on the dichotomized, composite primary outcome is based on an alpha level of 2.5% and a power of 73%.

